### Recruitment

Participants will be recruited over a 12-month period at 30 centre-based haemodialysis centres throughout the UK, including satellite units affiliated with main centres. All adult patients new to centre-based HD treatment will be screened using the trial eligibility criteria. Patients who start dialysis in a planned fashion will be approached in chronic kidney disease clinics at the point of deciding a convenient start date. Patients starting treatment that is unplanned will be approached at the point it is decided they will require long-term dialysis.

### Allocation

Both planned and unplanned incident HD patients will be randomized after informed consent has been obtained and at the point of commencing haemodialysis as an outpatient. Randomization will be 1:1 to the BI intervention and control groups, with random permuted blocks, stratified by centre (main or satellite where dialysis will commence.

Randomization will be during office hours using a secure centralized web-based, automated computer-generated randomization system provided by the Keele University Clinical Trials Unit (CTU). Authorized personnel at the trial site will be allocated personalized log-in details by Keele CTU to access this system. In the event the centre network is not functioning they will call the Keele CTU and authorized staff will perform the randomization on the centre’s behalf.

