**Methods/Design:**

516 pateints commencing haemodialysis, aged >18 with RKF of > 3 ml/min/1.73 m^2^ or a urine volume >500 ml per day or per the shorter inter-dialytic period will be consented and enrolled into a pragmatic, open-label, randomized controlled trial. The intervention is incorporation of bioimpedance spectroscopy (BI) determination of normally hydrated weight to set a post-dialysis target weight that limits volume depletion, compared to current standard practice. Clinicians and participants will be blinded to BI measures in the control group and a standardized record capturing management of fluid status will be used in all participants. Primary outcome is preservation of residual kidney function assessed as time to anuria (≤100 ml/day or ≤200 ml urine volume in the short inter-dialytic period). A sample size of 516 was based upon a cumulative incidence of 30% anuria in the control group and 20% in the treatment group and 11% competing risks (death, transplantation) over 10 months, with up to 2 years follow-up.

Secondary outcomes include rate of decline in small solute clearance, significant adverse events, hospitalization, loss of vascular access, cardiovascular events and interventions, dialysis efficacy and safety, dialysis-related symptoms and quality of life. Economic evaluation will be carried out to determine the cost-effectiveness of the intervention. Analyses will be adjusted for patient characteristics and dialysis unit practice patterns relevant to fluid management.

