#### Primary outcome

Time to anuria will be analysed on an intention-to-treat basis (as the primary analysis) and on an as-treated basis (as the secondary analysis) using competing risks survival analysis [32], to estimate the relative risk (as expressed by the sub-hazard ratio) of the outcome (anuria) in patients where BI is used compared to control patients, accounting for the competing risks (death, transplantation). Patients undergoing modality change or recovery will be censored at the point of treatment switch. The analysis will control for known baseline covariates affecting residual function [26, 29], i.e. age, race, sex, comorbidities (separately or using a validated scoring system), antihypertensive drug use (ACE inhibitors/ARBs, calcium antagonists) and diuretic use.

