#### Secondary outcomes

Difference in rate of decline in renal clearance will be analysed using a random slopes linear mixed model, with adjustment for baseline characteristics, as for the primary outcome. We will analyse the effect of randomization on fluid status and body composition as determined by BI (to ascertain the effect of the intervention on the fluid assessment decision) and undertake corresponding appropriate analyses of the other secondary outcomes such as (i) *dialysis-related symptoms and treatment efficacy* (e.g. inter-dialytic fluid gain, falls, post-dialysis recovery time), (ii) *critical events* such as cardiovascular events and interventions, access-related interventions/failures and death, and (iii) *patient-reported measures* (e.g. EQ-5D-5 L, SF-12, PAM, POS-S renal, CSRI CKD). In analysing the effect of the intervention on patient activation measures we will look to see if this is associated with objective measures of fluid management, e.g. inter-dialytic fluid gain which, following adjustment for comorbidity, is a surrogate measure of patient survival.

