Finally, in designing the trial we carefully considered the pros and cons of a cluster (dialysis unit) versus a patient-level randomisation. Apart from practical reasons (for example patients often transfer from the main dialysis unit to a satellite centre after initiation of treatment, potentially forcing either drop in or out of the intervention) we became aware of significant variation between sites in their approach to fluid management. We undertook a survey of UK dialysis units to establish this, confirming that the number of sites required to get a balanced cluster randomization would have been impractical [11]. We have, however, used the information from this survey to undertake an annual survey of practice patterns during the conduct of the trial to allow us to correct for these in the primary and secondary analyses. Understanding the interactions between these practice patterns and clinical outcomes are an additional, potentially useful benefit of the study.

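### Randomisation is stratified by centre, but the covariate set stated for the primary and clearance-slope models leaves centre out, and the article contradicts itself on unit-level adjustment

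*Protocol article*

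**What the plan says.** **Design.** The Allocation section uses blocks "with random permuted blocks, stratified by centre (main or satellite where dialysis will commence". The parenthesis is never closed, so centre could mean each dialysing unit or a main-versus-satellite split. Recruitment is planned at "30 centre-based haemodialysis centres throughout the UK, including satellite units affiliated with main centres".

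**Primary model.** Under Statistical methods, Primary outcome, a competing-risks model gives a sub-hazard ratio adjusted for known baseline covariates, "i.e. age, race, sex, comorbidities (separately or using a validated scoring system), antihypertensive drug use (ACE inhibitors/ARBs, calcium antagonists) and diuretic use". Centre does not appear as covariate, stratum, frailty or cluster.

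**Clearance slope.** Under Secondary outcomes, the model is a "random slopes linear mixed model, with adjustment for baseline characteristics, as for the primary outcome". Again no centre term is named.

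**Unit-level adjustment.** The abstract says: "Analyses will be adjusted for patient characteristics and dialysis unit practice patterns relevant to fluid management". The Discussion says the annual practice survey is there "to allow us to correct for these in the primary and secondary analyses". The Subgroup analyses section instead assigns unit practice patterns to an analysis of their own, and the primary-outcome section does not mention them.

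**Site differences.** Explaining the choice of individual randomisation, the Discussion reports: "we became aware of significant variation between sites in their approach to fluid management".

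**The concern.** Stratified blocks balance the arms within each centre. If centres differ in anuria risk, that balance removes the between-centre part of the chance variation in the treatment comparison. A model without centre does not know this: its standard error still allows for between-centre imbalance that the design has prevented. The interval is then wider than it needs to be and the test rejects less often than its nominal level. In a proportional-hazards model, omitting a prognostic factor also gives a marginal hazard ratio that lies closer to 1 than the centre-conditional one.

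The authors' own reasoning makes a centre effect plausible. Fluid management is the mechanism by which they expect kidney function to be lost, and they found that sites differ in it. At stake is some of the stated 90% power, in exchange for information that is already recorded for every patient.

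The second problem is that the article gives two answers on whether any unit-level term enters the primary model. An analyst could follow either and claim to be following the protocol.

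**Working it through.** **1. Reproduce the plan's figures.** Inputs from the Sample size section: 10-month anuria incidence 30% against 20%, competing events 11% (taken as the same in both arms), 90% power, 5% two-sided, 12 months' accrual plus 12 months' follow-up, 5% loss.

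With constant cause-specific hazards, the anuria hazard is (anuria share of all events) × (−ln(1 − total incidence))/10.
- Control: (0.30/0.41) × (−ln 0.59)/10 = 0.03861 per month.
- Intervention: (0.20/0.31) × (−ln 0.69)/10 = 0.02394 per month.
- Hazard ratio: 0.02394/0.03861 = 0.620.

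Schoenfeld's formula: 4 × (1.960 + 1.282)² / (ln 0.620)² = 42.03/0.2284 = 184.02, rounded up to **185 events**.

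The mean event probability over uniform follow-up of 12 to 24 months is 0.378. Then 185/0.378 gives 490, and 490/0.95 gives **516 patients**. Both figures reproduce exactly, and no centre term enters them.

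**2. Size of the strata.** Taking 30 units: 516/30 ≈ 17 patients and 185/30 ≈ 6 events per centre.

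**3. Effect of leaving centre out.** A simulation of 4,000 trials per setting used 516 patients, 30 equally likely centres, and a normal centre effect on the log hazard. It compared the log-rank test ignoring centre with the log-rank test stratified by centre. Assumptions not in the article: block size 4, the between-centre standard deviation (SD), and competing events treated as censoring. The hazard ratio was ln 0.8/ln 0.7 = 0.626.

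| Assumed SD | Type I error, centre ignored | Type I error, stratified | Power, centre ignored | Power, stratified | Power difference |
|---|---|---|---|---|---|
| 0 | 5.2% | 5.0% | 88.2% | 86.5% | −1.7 |
| 0.3 | 4.1% | 4.8% | 88.2% | 87.5% | −0.7 |
| 0.5 | 4.4% | 5.7% | 86.6% | 87.8% | +1.2 |
| 0.8 | 2.8% | 4.9% | 83.1% | 88.1% | +5.0 |

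Monte Carlo standard errors are about √(0.05 × 0.95/4000) = 0.3 points for type I error and √(0.88 × 0.12/4000) = 0.5 points for power.

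**4. Second check, with a Fine–Gray model.** This was smaller: 800 trials and 30 × 16 = 480 patients, with a standard error of about 1.2 points for each power.

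| Assumed SD | Centre ignored | Stratified | True centre effect included |
|---|---|---|---|
| 0.3 | 85.0% | 84.5% | 85.8% |
| 0.5 | 86.0% | 88.0% | 88.4% |
| 0.7 | 83.4% | 86.6% | 88.5% |

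At SD 0.5 to 0.7 the model standard error ignoring centre (0.153 to 0.155) exceeded the empirical SD of the estimate (0.147). The last column is an upper bound for a random centre effect, because no real analysis knows the true effects. No frailty model was fitted in either check.

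**5. The passages on practice patterns, side by side.** Abstract: analyses adjusted for them. Discussion: corrected for in primary and secondary analyses. Primary outcome: not listed. Subgroup analyses: separate. These cannot all describe the same primary model. Survey items also cannot capture every difference between centres, and the survey is repeated annually, so later rounds fall after many patients have been randomised.

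**The case against.** **How centre enters a model is normally left to the analysis plan, which is not shown.** This would settle the matter if the article were merely silent. It is not: it states the adjustment set, and the set omits centre. It is fair to answer that the list closes only the known baseline covariates affecting residual function, so a centre term could still be added elsewhere. The unseen plan may well do so. That lowers the weight of the point but does not remove the mismatch in the published text.

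**The authors do plan unit-level adjustment.** A reader might infer from the primary-outcome section that all unit-level adjustment is ruled out. The abstract and Discussion say otherwise, so that reading is too strong. What stands is that practice patterns are a partial proxy and that the article is inconsistent about them.

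**Variation in practice is not variation in anuria.** Correct. The Discussion reports differences in approach to fluid management and gives no between-centre variance for any outcome. Centre is plausibly prognostic, but not shown to be.

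**The inference is not broken.** Also correct. A reader might infer that the p-value is invalid or that false positives are inflated. In the simulation the error goes the other way: the test is conservative once centres differ. The marginal hazard ratio is a different estimand from the centre-conditional one, not a biased estimate of the treatment effect.

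**Stratifying can cost power.** At SD 0 to 0.3 full stratification lost about 0.5 to 2 points. This stands, and it determines the form of the fix.

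**Conclusion.** The point holds in a limited form. The stated covariate set omits the factor used to stratify randomisation, and the article disagrees with itself on whether unit practice patterns enter the primary model.

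The size depends wholly on an assumed between-centre SD of the log hazard: no power lost at 0 to 0.3, about 1 point at 0.5, about 5 points at 0.8, with type I error about 3% at 0.8. The larger figures need strong centre effects, and the 1-point figure is small against simulation error. The results also rest on 30 equal-probability centres, blocks of 4 and a cause-specific log-rank test. The Fine–Gray check points the same way.

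It would be wrong to attribute the whole gap between the simulated powers and 90% to centre. With no centre effect the simulated power is already 88.2%, partly because the simulation used a hazard ratio of 0.626, for which 185 events give 89.1%. The sample size itself is sound on its own assumptions. The effect on the clearance slope was not quantified, because the article gives no SD for that outcome.

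This is worth correcting because it costs little, not because the trial's conclusion would otherwise be unsafe.

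**What to change.** 1. State that the primary model includes centre as randomised, preferably as a shared frailty or random centre effect. Use the centre at randomisation, since the Discussion notes that patients often transfer from main to satellite units. Set in advance the rule for pooling small satellites with their parent centre. Avoid 29 fixed effects or full stratification with about 6 events per centre.
2. Add a random centre intercept to the linear mixed model for clearance.
3. Close the parenthesis in the Allocation section so that it is clear what defines a stratum.
4. Reconcile the abstract, Primary outcome, Subgroup analyses and Discussion: say either that practice patterns enter the primary model, naming the items and the survey round, or that they are only a separate exploratory analysis.

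**Cost.** Wording only, with no new data and no change to 516 patients or 185 events. The modelling is slightly more complex, and the reported sub-hazard ratio becomes conditional on centre, which should be stated. Full stratification would cost about 0.5 to 2 points of power if centres hardly differ. A random effect should largely avoid that, though this was not simulated directly. If the analysis plan already handles centre, aligning the protocol text is all that is needed.

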### Blinding

BI readings will be taken in both study groups but the results concealed from the clinical teams and patients in the controls. To ensure blinding to BI data in control subjects and to minimize performance bias, BI measurements will be taken independently from clinical fluid assessments by the research nurse. The full BI dataset will be stored for all patients using the proprietary software, but in the BI intervention arm the key BI metrics used for informing the clinical decision will be transferred to the clinical assessment CRF (BISTRO study intervention record) prior to their use.

### Data collection: methods and management

#### Demographic data, clinical and bioimpedance assessments of fluid status

Data at baseline and subsequently (see Table 1) will be collected on paper CRFs at the specified time intervals – with the option of recording additional fluid assessment if clinically indicated (e.g. following hospital admission). Fluid assessments are recorded on the BISTRO study intervention record, onto which the BI-determined normally hydrated weight is transferred in the intervention group only (see Fig. 2). Electronic capture of a full bioimpedance dataset is supported by the device software and stored on the dialysis unit server for later transfer to the CTU.

**Fig. 2 Fig2:**
[figure not shown]
BISTRO fluid assessment record. At each fluid assessment the clinician will complete this chart, recording any target weight adjustment, planned interventions to achieve this and any factors that have influenced their decision to set or override the suggested target weight. Only in the those patients randomised to the intervention will the normally hydrated weight post dialysis be completed and thus available to the clinician

#### Residual kidney function

This is determined from a urine collection and routinely collected blood samples for urea and creatinine. The research nurse will enter these data into a GFR calculator to calculate residual kidney function. The whole procedure will be carried out in accordance with a study-specific standard operating procedure for measurement of residual renal function in haemodialysis patients by the Leeds Teaching Hospitals NHS Trust and adapted for the BISTRO trial.

#### Patient reported outcomes

These will be administered using a patient booklet containing the items listed in Table 1. The Montreal Cognitive Assessment (MoCA) will be administered by research nurses who have received training.

#### Unit-level survey of practice patterns

A unit-level survey will be completed annually for the project duration by the Lead Consultant for each dialysis Unit (see Table 2 for items).

**Table 2 Tab2:** Unit level practice patterns, measured annually: first completion just before the first patient is enrolled

Dialysate sodium concentration
• Is there a standard sodium concentration in your unit? • What is the concentration of sodium used most frequently? • What proportion of patients have an individualised sodium concentration? • If individual sodium used o If low, what reason? If high, what reason? o Is your practice to match the plasma sodium?
Nutrition and sodium intake
• Does your HD unit have a dedicated dietitian? If so, how much time per patient do they have? • Do you have a policy on sodium restriction? If so what is the advised intake? • Do you have a policy on fluid restriction? If so what is the advised intake? • What information/training is given to nurses on the HD unit about fluid/salt restrictions? • Are patients given written advice about dietary intake and restrictions?
Diuretics
• Are the majority patients with residual kidney function routinely prescribed loop diuretics? • What is the typical dose (e.g. Furosemide, Bumetanide)? • Do you routinely use other diuretics (metolazone, thiazides, aldosterone inhibitors)?
Incremental dialysis
• Is it routine practice in your unit to commence HD incrementally? • If so, is this to preserve residual kidney function? • What proportion of patients on your unit do (a) 1 or (b) 2 sessions per week in the context of incremental start?
Measurement of residual Kidney Function
• Do you routinely measure residual kidney function on your unit? If so how frequently? • If so, do you use this to reduce the (a) frequency, (b) length of dialysis sessions?
Assessment and prescription
• Do you have a standardised protocol for assessing fluid status in new HD patients? • Protocol or not, in addition to clinical assessment do you routinely use (a) bioimpedance – of so state device, (b) Chest Xray,(c) Echocardiogram (d) central vein diameter, (e) blood volume monitoring? • Who assesses fluid status on your unit (a) consultants (b) HD dedicated staff grades (c) HD nurses (d) training grade doctors.
Fluid management strategies
• Who prescribes fluid management on your unit (a) consultants (b) HD dedicated staff grades (c) HD nurses (d) training grade doctors. • Do you have a policy to maximise UF rates in your unit? If so, what is the maximum rate permitted? • If you are changing the target weight, typically what is the maximum change per session you would prescribe? (Exclude urgent situations and tell us if there is no specific policy on this).

#### Routine clinical data collected by the UK Renal Registry

Routine clinical data collected by units for the Renal Registry returns will be transferred to the CTU for incorporation into the trial database annually (2017, 2018 and final download at study end) in the form of an electronic download (following appropriate testing procedures to ensure data integrity). This includes data collected for individual dialysis sessions (e.g. pre- and post-dialysis weights and blood pressures, dialysis prescription), haematology and biochemistry results, and treatment modality timelines, using the Renal Registry Dataset V4.2 (www.renalreg.org). If sites are not providing this information as part of their routine submission to the UKRR then they will be required to send a separate file with the fields by an appropriate secure mechanism to the UKRR at least once at the end of the trial. Admission and discharge dates, diagnostic and procedural codes will be obtained from Hospital Episodes and Statistics (or its equivalent body) by data linkage. If subjects choose to drop out of the study they will asked if they are still willing for their routine data be used (this is consented for independently).

### Statistical methods

Analysis will be in accordance with a predetermined statistical analysis plan and will be conducted blind to treatment allocation. Statistical significance will be set as *p* ≤ .05 (two-tailed).

#### Primary outcome

Time to anuria will be analysed on an intention-to-treat basis (as the primary analysis) and on an as-treated basis (as the secondary analysis) using competing risks survival analysis [32], to estimate the relative risk (as expressed by the sub-hazard ratio) of the outcome (anuria) in patients where BI is used compared to control patients, accounting for the competing risks (death, transplantation). Patients undergoing modality change or recovery will be censored at the point of treatment switch. The analysis will control for known baseline covariates affecting residual function [26, 29], i.e. age, race, sex, comorbidities (separately or using a validated scoring system), antihypertensive drug use (ACE inhibitors/ARBs, calcium antagonists) and diuretic use.

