The introduction of bioimpedance (BI) technology, such as BI spectroscopy, provides clinicians with the opportunity to break this cycle while avoiding the risk of excessive overhydration. BI gives additional information about body composition available at the bedside [12]. The principle is simple and involves the passing of a low-strength alternating current through the subject’s body to measure the resistance and reactance to flow. These two measures are dependent on the amount of fluid and cell membranes between the electrodes (usually placed on the hand and foot on one side of the body). The measurements are then modelled using information such as the subject’s weight and height to estimate the total volume of fluid in the body and the proportion of this that is within cells or in the extracellular space. In dialysis patients, compared to healthy subjects, the total amount of fluid (intra plus extracellular) can be high or low, but often the latter because of muscle wasting, inflammation or even over-aggressive fluid removal on dialysis. However, if the extracellular fluid is disproportionately high, this is a strong signal for an increased mortality risk [13–15]. For this reason, until now trials conducted to establish the clinical value of BI in setting target weights have focussed on clinical endpoints associated with hypervolaemia, such as high blood pressure, left ventricular mass and pulse- wave pressure or worsening extracellular to intracellular fluid distribution. The results of these interventions have been mixed, and more trials are clearly needed, but the price for achieving lower blood pressure through post-dialytic hypovolaemia was accelerated loss of RKF in one such study [16]. There is also evidence that presence of RKF leads to more stable fluid status without intervention in peritoneal dialysis patients [17]. Thus, BISTRO will establish the potential for BI to add value to fluid management and address the concern that this technology may be being adopted indiscriminately without clear evidence of benefit and a potential risk of harm.

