## Methods/Design

### Aim

To determine if incorporation of bioimpedance spectroscopy-derived information on body composition into the setting of the post-dialytic target weight reduces loss of residual kidney function in incident centre-based HD patients, with the potential to improve clinical outcomes, dialysis-related symptoms, hospitalization and survival.

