### Outcomes

**Primary Outcome: Preservation of Residual Kidney Function**
Time to anuria, defined as urine volume ≤100 ml/day or ≤200 ml in the short inter-dialytic period confirmed by a further collection after 2 weeks to exclude temporary illness.

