### Sample size

#### Primary outcome (time to anuria)

It can be determined from cohort studies and data collection from a large dialysis unit of 615 patients that the proportion of incident centre-based HD patients anuric by 10 months is in the region of 30% (range 25–67%) [26–30]. Sample size is based on a cumulative 10-month incidence of anuria of 30% in the control group and 20% in the treatment group and 11% competing risks (based on death and transplantation data extrapolated from the 2013 UKRR report [31]). Assuming exponential decline, proportional hazards, 90% power and 5% two-tailed significance, 185 events are required to detect the corresponding hazard ratio, with 12 months accrual and 12 months follow-up. This will require a total of 516 patients to be randomized 1:1, allowing for a 5% loss to follow-up.

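### The primary outcome is labelled preservation of kidney function, but its only effect measure, the sub-hazard ratio, also moves with death and transplantation, and the sample size matches a different ratio

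*Protocol article*

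**What the plan says.** The Outcomes section of the protocol article heads the primary outcome "Primary Outcome: Preservation of Residual Kidney Function" and defines it as time to confirmed anuria.

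Under Statistical methods, Primary outcome, a competing risks survival analysis is to give a relative risk "as expressed by the sub-hazard ratio) of the outcome (anuria) in patients where BI is used compared to control patients" (BI is bioimpedance), "accounting for the competing risks (death, transplantation". The same measure serves the intention-to-treat and the as-treated analysis. Other exits are handled differently: "Patients undergoing modality change or recovery will be censored at the point of treatment switch". No other effect measure is named for the primary outcome.

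On competing events, the Background says that "if the extracellular fluid is disproportionately high, this is a strong signal for an increased mortality risk", and the Aim describes the intervention as having its kidney effect "with the potential to improve clinical outcomes, dialysis-related symptoms, hospitalization and survival".

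The Sample size section states: "Sample size is based on a cumulative 10-month incidence of anuria of 30% in the control group and 20% in the treatment group". It adds 11% competing risks (death and transplantation), 90% power, 5% two-tailed significance, 185 events, 12 months of accrual plus 12 months of follow-up, 5% loss, and 516 patients randomized 1:1.

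**The concern.** In a sub-hazard model a patient who dies or is transplanted before anuria stays in the risk set as someone who has not become anuric. The ratio therefore carries two things at once: the effect on losing urine output and the effect on leaving by death or transplant. If competing events are equally frequent in both arms this matters little. The Aim, however, hopes that the intervention changes survival, so equality cannot be taken for granted.

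Two misreadings are possible. If BI guidance did nothing for the kidney but more BI patients died or were transplanted before anuria, the ratio would fall below 1 and look like preservation. If BI improved survival, as hoped, the ratio would move towards 1 and understate a real kidney benefit, with a loss of power. The outcome label invites a statement about the kidney that the named measure cannot support unaided.

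**Working it through.** **Inputs (Sample size section).** 10-month cumulative incidence of anuria 30% (control) and 20% (BI); competing risks 11%, taken as the same in both arms because one figure is given; follow-up 12 to 24 months, uniform; 516 patients less 5% = 490 evaluable. Constant hazards, no covariates.

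**Step 1: cause-specific hazards per month.** Total hazard = −ln(1 − anuria − competing)/10, split in proportion to the two incidences.
- Control: −ln(0.59)/10 = 0.05276; anuria × 30/41 = 0.03861; competing × 11/41 = 0.01416.
- BI: −ln(0.69)/10 = 0.03711; anuria × 20/31 = 0.02394; competing × 11/31 = 0.01317.
- Cause-specific ratio for anuria: 0.02394/0.03861 = 0.620.

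**Step 2: reproduce the stated figures.** Schoenfeld events = 4(1.960 + 1.282)²/(ln HR)².
- HR 0.620: 42.03/0.2284 = 184.02, rounded up to 185.
- Mean probability of observed anuria over 12–24 months: 0.3777. Then 185/0.3777 = 490, and 490/0.95 = 516.

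Both stated figures reproduce. Other routes do not give 185: ln(0.8)/ln(0.7) = 0.626 gives 192 by Schoenfeld and 199 by Freedman; Freedman at 0.620 gives 192; a common competing hazard (ratio 0.624) gives 189.

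**Step 3: the sub-hazard ratio implied by the same assumptions.** Solving the expected Fine–Gray score equation with uniform 12–24 month censoring gives a limiting value of 0.633. Power with 185 events: Φ(√(185/4) × |ln 0.633| − 1.96) = Φ(3.11 − 1.96) = 87.5%; given the approximations, read this as 86–88%. For scale, 90% power at 0.633 needs 42.03/0.2092 = 201 events.

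**Step 4: no kidney effect (cause-specific ratio for anuria 1.00), competing hazard on BI varied.**

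| Competing hazard, BI : control | Competing events on BI at 10 months | Sub-hazard ratio | Chance of a significant false benefit (nominal 2.5%) |
|---|---|---|---|
| 0.5 | 5.7% | 1.07 | 0.7% (false harm 7.3%) |
| 0.75 | 8.4% | 1.03 | 1.4% |
| 1.25 | 13.5% | 0.97 | 4.3% |
| 1.5 | 16.0% | 0.94 | 6.9% |
| 2 | 20.6% | 0.88 | 14.8% |

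**Step 5: planned kidney effect (cause-specific ratio 0.62).**

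| Competing hazard, BI : control | Sub-hazard ratio | Power, sub-hazard | Power, cause-specific |
|---|---|---|---|
| 0.5 | 0.669 | 79% (78% at exactly 185 events) | 91% |
| 0.7 | 0.652 | 83% | 90% |
| 1 | 0.627 | 89% | 90% |
| 1.5 | 0.589 | 94% | 89% |

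The 0.627 here differs from 0.633 in step 3 because equal competing hazards are not quite the same as 11% competing incidence in both arms.

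**The case against.** The strongest reply is that the article names a legitimate estimand, frames its planning in cumulative incidence, and defers to a statistical analysis plan that is not shown and could add cause-specific ratios. That is right about legitimacy: the sub-hazard ratio is a valid measure of the effect on the incidence of anuria. The absence of supporting analyses would not be a point by itself. What remains is that the article itself fixes both the measure and the label, and sizes the trial on a ratio other than the one it analyses.

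Second, the ratio does not stand alone in the trial. The slope of urea and creatinine clearance is a secondary outcome with stated power of just under 95%, and death is analysed as a secondary event. This stands: excess deaths or an unchanged slope would be visible. But neither is tied to the reading of the primary ratio, and transplantation is not listed as an outcome.

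Third, the imbalances are assumed. The 11% mixes death and transplantation, and the article gives no reason for BI to change transplantation. If deaths are 50–70% of the total (an assumption) and transplantation is unaffected, doubling the composite needs a death hazard 1 + 1/0.7 = 2.4 to 1 + 1/0.5 = 3 times control. Halving it needs a cut of 0.5/0.7 = 71% to 100%. This also stands, and it limits the size of the point.

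Fourth, the cause-specific ratio conditions on being alive and untransplanted, so it is not a pure kidney effect either. That is why it should be read with the clearance slope.

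A reader might infer that the sub-hazard ratio is the wrong analysis, or that the trial is set to report excess deaths as kidney preservation. The documents support neither. The Background sentence on extracellular fluid concerns overhydration as a risk marker and does not say that BI raises mortality; the Aim anticipates better survival, which would make the ratio conservative.

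**Conclusion.** The point holds in a limited form. The only measure named for the primary outcome mixes the effect on urine output with any effect on death or transplantation, while the outcome is labelled as preservation of kidney function.

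The distortion is modest for small imbalances and becomes material at a doubling of competing events. The likelier cost, given the hope of better survival, is lost power: about 83% if competing events fall by 30% and 78–79% if they halve, where a cause-specific test keeps about 90%.

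Separately, and without any assumed imbalance, 185 events give 90% power for a cause-specific ratio of 0.62 but about 86–88% for the sub-hazard ratio to be analysed. That gap is small. It is a mismatch between planning and analysis and does not show that the trial is seriously undersized.

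All figures assume constant hazards, uniform accrual and no covariate adjustment.

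**What to change.** Keep the sub-hazard ratio as the primary measure. In the analysis plan:

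1. Pre-specify beside it the cause-specific hazard ratios for anuria, death before anuria and transplantation before anuria, with the same covariates, and the cumulative incidence of each by arm.
2. Describe the sub-hazard ratio as the effect on the incidence of anuria.
3. Base any statement about a direct effect on residual kidney function on the cause-specific ratio for anuria, read together with the clearance slope.
4. State that the 185 events were derived from the cause-specific ratio, and give the power for the sub-hazard ratio.

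Do not make the claim depend on formal agreement between the two ratios in direction and size: such a rule has no threshold and would put a subjective gate on the primary result.

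The cost is a few extra model fits on data already collected and a slightly more cautious headline. Design, sample size and clinical conduct are unchanged.
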